### 2.8. Endpoint

#### 1.2.8. Primary outcome.

The success rate on the first attempt will be considered as the dependent variable. Insertion success will be defined as the successful passage of the tube on the first attempt and confirmed by radiography of the correct anatomical positioning of the tube distal tip, which will be performed immediately after the procedure. If the nasally placed small-bowel feeding tube is not successfully inserted, it will be considered a failure and recorded as an unsuccessful attempt. Subsequently, new attempts will be performed.

The number of attempts required for successful insertion will be recorded for each patient. It should be noted that if more than 3 attempts are required, the procedure will be declared unsuccessful and data will be used to count failures. In these cases, the researchers may use another method of free choice for nasally placed small-bowel feeding tube insertion.

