#### 2.2.8. Secondary outcome.

Secondary endpoints will be time required and associated complications. The time required will be recorded from the nasally placed small-bowel feeding tube insertion from the nostril to the calculated length of the tube with the aid of a stopwatch. The insertion times for each attempt will be counted and, in case of failures, the time required for each attempt will be added together.

In addition, AEs associated with the insertion techniques (bleeding of the visible mucosa, nasal mucosa edema, in addition to tube bending, twisting, knotting and insertion into the trachea visible on X-ray) will be recorded. It is noteworthy that the occurrence of bleeding will be considered as visible bleeding in the tube extension and nasal or oral mucosa. The analysis of such AEs will be performed immediately at the end of the procedure until radiological confirmation of the tube positioning and previous removal of the guide wire. The radiograph will be performed on the patient bed and the patient will be kept in the same position, in the supine position. If the patient shows signs of respiratory distress during insertion, the procedure will be stopped.

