### 2.10. Randomization and masking

Thirty-nine patients will be randomly divided into 3 groups. Patients allocated in the control group (CG) will have the tube inserted in the conventional way, that is, the head is kept in the neutral position, while the tube is gently inserted through one of the nostrils, without any maneuver or instrument.

Patients selected for the first intervention group (GI1) will have their heads turned to the right lateral position. This way, the tube will be inserted through the selected nostril without any neck maneuver or instrument.

For patients selected for the second intervention group (GI2), a conventional adult laryngoscope will be orally inserted. The tracheal tube and tongue will be raised to provide the best view of the larynx area. Thus, after viewing the piriform sinus or the esophagus, the tube will be inserted into the patient nostril and advanced to the esophagus under direct visualization. The patient head will be held in the neutral position and the blade will be gently lifted to avoid excessive neck extension.

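### Bleeding is scored on visibility but not limited to signs that can be seen alike in every patient, so its detection may depend partly on placement failure and on arm

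*Protocol article*

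**What the plan says.** All places are in the protocol article.

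- **Definition (2.2.8, Secondary outcome).** The list of adverse events opens with "bleeding of the visible mucosa, nasal mucosa edema, in addition to tube bending, twisting, knotting". The next sentence widens the bleeding item: "the occurrence of bleeding will be considered as visible bleeding in the tube extension and nasal or oral mucosa". The tube appears only in the second wording. Its joining word, read literally, would require blood at both places; either place is the natural reading.
- **Timing (2.2.8).** "The analysis of such AEs will be performed immediately at the end of the procedure until radiological confirmation of the tube positioning". The Abstract, however, presents mucosal bleeding among the complications that arise during insertion.
- **Failed attempts (1.2.8, Primary outcome).** When the tube is not placed, "it will be considered a failure and recorded as an unsuccessful attempt. Subsequently, new attempts will be performed". There is a ceiling: "if more than 3 attempts are required, the procedure will be declared unsuccessful and data will be used to count failures".
- **Techniques (2.10).** In the control group the tube goes in "without any maneuver or instrument", and GI1 likewise uses no instrument. In GI2 "a conventional adult laryngoscope will be orally inserted", and "the tube will be inserted into the patient nostril and advanced to the esophagus under direct visualization".
- **Masking (2.6).** Only the data analysts are blinded, so whoever records bleeding knows the arm.

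**The concern.** The definition names three places to look: the tube, the nasal mucosa and the oral mucosa. They are not equally open to view in every patient. A correctly placed tube remains in the patient throughout the stated assessment window, so its inserted length cannot be inspected. A tube that failed and was pulled out can be. The mouth and pharynx are seen through a laryngoscope in GI2 and in no other arm.

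Complications are part of the trial's null and alternative hypotheses (Introduction), and bleeding is one of the listed complications that is an injury to the patient. If the chance of seeing a bleed differs by arm, the difference in recorded bleeding mixes injury with opportunity to observe it. If that chance also rises with failed attempts, part of the bleeding result would echo the primary outcome. An unblinded recorder working without a standard inspection gives no protection against either.

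**Working it through.** The plan states no bleeding rate, so there is no figure to reproduce. The check has two parts.

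**1. What can be seen, by site**

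- *Nasal mucosa and the tube outside the nostril:* visible in every patient and arm.
- *Inserted part of the tube:* hidden after success; visible after failure if the tube is withdrawn. Withdrawal is implied by the new attempts. Neither withdrawal nor inspection of the withdrawn tube is stated.
- *Oral mucosa:* named for all patients, but no manner of inspection is given. A laryngoscopic view exists in GI2 only.

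Detection can therefore differ by failure and by arm, but only in part, because the nasal route is open to all.

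**2. Illustration of size**

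Let p be true bleeding (equal in all arms), m the share of bleeds visible without withdrawing a tube, and f the share of patients with a withdrawn tube. Assume that a bleed not otherwise visible is always seen on a withdrawn tube. Then

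recorded rate = p × (m + (1 − m) × f).

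The one input from the documents is first-attempt failure in the study cited in the Introduction: (104 − 86)/104 = 17.3%. All values of p and m, and the other values of f, are assumptions.

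*(a) Better view in GI2, same failure everywhere* (p = 0.20, f = 0.173):
- GI2, m = 0.8: 0.20 × (0.8 + 0.2 × 0.173) = 16.7%
- Blind arms, m = 0.5: 0.20 × (0.5 + 0.5 × 0.173) = 11.7%; ratio 1.4
- Blind arms, m = 0.3: 0.20 × (0.3 + 0.7 × 0.173) = 8.4%; ratio 2.0

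*(b) Upper limit on the view: GI2 detects every bleed* (p = 0.30, so GI2 records 30%):
- Blind arms, m = 0.5: 18% at f = 0.2 and 21% at f = 0.4; ratios 1.7 and 1.4
- Blind arms, m = 0.7: 22.8% and 24.6%; ratios 1.3 and 1.2

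*(c) Laryngoscope shows half of the otherwise hidden bleeds, no withdrawals in GI2* (p = 0.30, m = 0.5):
- GI2: 0.30 × (0.5 + 0.5 × 0.5) = 22.5%, against 18% in blind arms with f = 0.2; ratio 1.25

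*(d) Failure route alone* (p = 0.20, same m in both arms, f = 0.50 against 0.05):
- m = 0.3: 13.0% against 6.7%; ratio 1.94
- m = 0.5: 15.0% against 10.5%; ratio 1.43
- m = 0.8: 18.0% against 16.2%; ratio 1.11

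Here the excess goes to whichever arm fails more.

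*(e) Both routes, opposed* (p = 0.20):
- GI2 with m = 0.8, f = 0.05: 16.2%. Blind arm with m = 0.5, f = 0.50: 15.0%. Ratio 1.08, so they nearly cancel.
- With no view advantage (m = 0.5 in both) and fewer failures in GI2: 10.5/15.0 = 0.70, so the direction reverses.

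**Scale in patients.** Taking the 39 patients as three groups of 13, case (a) is 0.167 × 13 = 2.2 recorded bleeds in GI2 against 1.1 to 1.5 in a blind arm. In case (b) with m = 0.5, doubling withdrawals from 20% to 40% adds 0.03 × 13 = 0.4 of a patient.

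**Effect on testing.** At 13 per arm, the two-sided Fisher test at 5%, applied to the failure route alone (f = 0.50 against 0.05, p = 0.20 to 0.40, m = 0.3 to 0.5), rejects in 0.8% to 4.8% of trials. With both arms at p it rejects in 1.4% (p = 0.20) or 2.6% (p = 0.40). The issue is a distorted estimate, not a large excess of false positives.

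**The case against.** The strongest reply is that 2.2.8 sets one assessment window for all arms, after the procedure, whereas the laryngoscopic view and the withdrawal of a failed tube occur during it. The section also names oral mucosa for every patient, so the mouth may well be examined in all arms. The phrase about no instrument in the control group describes insertion, not assessment. The term used for the tube may mean only its visible length. The article also mentions a script for each technique and a printed form, neither of which is shown, and details of inspection could sit there.

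Much of this stands, and it reduces the asymmetry. It does not remove it. The bleeding sentence is not limited to what is seen inside the window, and the Abstract counts complications of insertion itself. Blood noticed on a withdrawn tube or through the blade could therefore be scored, and nothing in the text says that it should not be.

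Two further replies also stand. Repeat attempts can injure, so a link between failure and bleeding may be real harm. And a comparison restricted to equally visible signs gives up some sensitivity, so bleeding from all sources must still be reported.

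A reader might infer that bleeding is found only when placement fails, or that the rule is bound to make laryngoscopy look more traumatic than it is. The documents support neither. Nasal bleeding is visible in every arm, inspection of withdrawn tubes is an inference, and fewer failures in GI2 would pull the other way.

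**Conclusion.** The point holds in a limited form: as written, the opportunity to see a bleed may differ partly by placement failure and by arm, and no stated step equalises it. The ratio of about 1.2 to 2.0 for GI2 against the blind arms comes from cases (a) to (c), which let the better view in GI2 act without an opposing difference in failure strong enough to cancel it. It is not a bound: case (e) gives 1.08 and 0.70. Neither the size nor the net direction can be derived from the documents, which give no bleeding rate, no share visible on the mucosa and no withdrawal share. It would also be too strong to say that the bleeding result merely repeats the primary result, because extra attempts can cause true bleeding. Severity is minor: one component of a secondary outcome.

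**What to change.** In 2.2.8, use one wording for bleeding and base the between-arm comparison on one inspection done the same way in every patient: nostrils and mouth viewed with a light, without a laryngoscope, after the last attempt with the assigned technique and before the X-ray, scored yes or no.

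Add two form fields: blood seen only on a withdrawn tube, and blood seen only through the laryngoscope. Report these by arm, and also report total visible bleeding from any source by arm, so that no injury is dropped.

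Because data collection is already under way (2.1), record the date of the change and show bleeding before and after it.

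The cost is a revised definition, two form fields and a few seconds at the bedside for the observer already present. The downside is a main bleeding comparison that is somewhat less sensitive; the all-source total reported beside it covers what that comparison leaves out.

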## 1. Introduction

According to the World Health Organization, 1 in 10 patients experience unnecessary harm as a consequence of unsafe health care assistance, which in more extreme situations, can cause the patient death.^[1]^ In this context, patient safety is related to a set of activities that aim to mitigate risks to an acceptable minimum, make the error less likely and, when it occurs, reduce the impact^[2]^ prevents the occurrence of adverse events (AEs) or injuries resulting from health procedures.^[3]^

In this context, despite being a common procedure, nasally placed small-bowel feeding tube insertion is not risk-free and can compromise patient safety. Due to the fact that nasally placed small-bowel feeding tube is commonly inserted ‘“blindly,” with the patient head in the neutral position, sometimes the process becomes difficult and traumatic, and may present higher level of complexity in physiological or induced coma and intubated patients, as the tongue displaced backwards blocks the passage through the pharynx. In addition, the piriform sinus and the arytenoid cartilage are considered anatomical obstacles for the nasally placed small-bowel feeding tube passage, which is sometimes bended in the oral cavity due to the inability to swallow and the presence of the endotracheal cannula cuff.^[4]^

Therefore, AEs such as accidental tube displacement, wrong positioning in the respiratory tract, tube obstruction, inadvertent exit, bronchoaspiration and connection route errors can occur during this procedure.^[5,6]^ Among serious and fatal AEs, pneumothorax, aspiration pneumonia and pulmonary hemorrhage stand out.^[7,8]^

There are different nasally placed small-bowel feeding tube insertion methods in critically ill and/or coma patients, which, although less common, have high procedural success rates, but none of them is perfect or universally accepted.^[9,10]^ It is noteworthy that the choice of techniques for this study was based on high success rate, low cost, availability and the lack of need to remove the patient from the Intensive Care Unit (ICU).^[11–14]^

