Results favorable to the use of different nasally placed small-bowel feeding tube insertion methods have been described by anesthesiologists.^[11–13]^ Among these, the lateralized head^[5,12]^ and the use of the laryngoscope^[11]^ stand out. Such studies have demonstrated nasally placed small-bowel feeding tube insertion methods that are faster, more effective and that cause less complications to patients. However, it is clear that such techniques are little used by nurses in clinical practice. It is important and necessary for nurses to be able to offer safer care with less risk of complications, based on the best available evidence, through the possibility of revealing the most adequate, effective, fast and safe technique to improve the execution of this procedure.

In a study conducted in Taiwan, 130 insertion attempts were performed. The success rate was 82.7% (86 of 104 patients) on the first attempt and 100% in 5 attempts. In 23 patients the tube deviated to the oral cavity and 3 to the trachea.^[15]^ Verification of vital signs are important to detect clinical deterioration of the patient.^[16]^

We seek to test the following hypothesis: null hypothesis: There are no significant differences between the methods of insertion of the nasally placed small-bowel feeding tube in patients in coma (physiological or induced) and intubated in relation to the rate of success in the first attempt, insertion time and the presence of complications; alternative hypothesis: There are significant differences between the methods of nasally placed small-bowel feeding tube insertion in comatose patients (physiological or induced) and intubated in relation to the rate of success in the first attempt, insertion time and the presence of complications.

Therefore, the study aims to determine the effectiveness of different nasally placed small-bowel feeding tube insertion techniques in coma and intubated patients, in comparison with conventional method.

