### 2.11. Data collection

A data collection printed form containing variables about patients will be used, namely: Identification (bed; name initials; age; sex; date of birth); Clinical data (cause of admission; estimated weight, height and body mass index); Level of consciousness or Ramsay scale data, including type of drug used and sedation duration; Endotracheal tube number and cuff pressure; Data regarding the technique used (technique; number of attempts; required time in seconds; complications, if any); Parameters to be evaluated (heart and respiratory rate, blood pressure and oxygen saturation) before, during and after nasally placed small-bowel feeding tube insertion using each of the techniques; Confirmation of the correct nasally placed small-bowel feeding tube positioning by chest and abdomen radiography in bed.

Table 1 shows the detailed study stages, with the Standard Protocol Items for Randomized Trials schedule of enrollment, interventions, and assessments.

**Table 1 T1:** Description of the study stages: P1: Day 1—request for nasally placed small-bowel feeding tube insertion in the patient and intervention. F1: evaluation after the procedure until X-ray is performed.

Study period					
			Post-allocation: Allocation, interventions, follow-up		
Timepoint	Enrollment	Baseline	Allocation	P1 intervention	Follow-up (F1)
Enrollment:					
Eligibility criteria	X				
Recruitment	X				
Initial assessment	X				
Informed consent	X				
Allocation			X		
Interventions:					
Insertion in a conventional manner (control group)				⟷	X
Insertion with the head turned to the right side (intervention group)				⟷	X
Insertion with laryngoscope (intervention group)				⟷	X
Assessments:					
Identification, clinical data, level of consciousness, SSVV, among others		X			

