## 3. Discussion

The analysis of the effectiveness of different nasoenteral tube insertion techniques in coma (physiological or induced) and intubated patients is initially necessary due to the difficulty of inserting small-bowel feeding tube in a blind manner, with the patient head in the neutral position. The high rate of complications resulting from the small-bowel feeding tube insertion due to the absence of a proven safer method poses a risk to the patient.

A randomized clinical trial emphasizes that the small-bowel feeding tube insertion is often a challenge for ICU professionals. Therefore, the use of instruments that help through visualization was also reported as a facilitator for tube insertion and proper small-bowel feeding tube positioning in critically ill patients, such as laryngoscopes and videolaryngoscopes. Radiological and endoscopic techniques and methods guided by electromagnetism and fluoroscopy will also be used.^[13]^

Therefore, it is important and necessary to offer safer care with less risk of complications based on the best available evidence for the possibility of revealing the most adequate, effective, fast and safe technique to improve the performance of this procedure.

In addition, there is the possibility of characterizing nursing care based on new techniques in order to be used in clinical practice and to expand the knowledge base and skills of nurses in managing the small-bowel feeding tube insertion in critically ill patients, being an accessible and low-cost technology that can be used by nurses, streamlining work processes and contributing to adequate, safe and quality care.

Results favorable to the use of different nasoenteral tube insertion methods have been described by anesthesiologists.^[14–16]^ Among these, the lateralized head^[4,15]^ and the use of the laryngoscope^[4]^ stand out. Such studies have demonstrated small-bowel feeding tube insertion methods that are faster, more effective and that cause less complications to patients.

However, it is clear that such techniques are little used by nurses in clinical practice, in addition to a gap related to the deficiency of experimental studies with high level of evidence in relation to new small-bowel feeding tube insertion techniques to aid decision-making in clinical practice, which justifies the conduction of the present study.

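### The complication endpoint stops at the immediate X-ray and does not list the three serious events the protocol names, so it supports a conclusion on immediate insertion complications but not an unqualified one on the safe technique

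*Protocol article*

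**What the plan says.** **Recorded events.** Section 2.2.8 makes complications a secondary endpoint. The list starts with visible mucosal bleeding and continues: "nasal mucosa edema, in addition to tube bending, twisting, knotting and insertion into the trachea visible on X-ray) will be recorded". Bleeding is defined as what can be seen along the tube or on the nasal or oral mucosa. The Abstract's list of complications is no broader.

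**Window.** Section 2.2.8: "The analysis of such AEs will be performed immediately at the end of the procedure until radiological confirmation of the tube positioning". Section 1.2.8 says of the radiograph: "which will be performed immediately after the procedure". The legend of Table 1 (section 2.11) gives the same end: "F1: evaluation after the procedure until X-ray is performed".

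**Known risks.** The Introduction says: "Among serious and fatal AEs, pneumothorax, aspiration pneumonia and pulmonary hemorrhage stand out". It also names bronchoaspiration and misplacement into the airway.

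**Use of the result.** Both hypotheses compare the methods "in relation to the rate of success in the first attempt, insertion time and the presence of complications". The formal aim is narrower: "the study aims to determine the effectiveness of different nasally placed small-bowel feeding tube insertion techniques". The Introduction and the Discussion both speak of the possibility of "revealing the most adequate, effective, fast and safe technique".

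**Other data.** The form in section 2.11 has an open entry for complications. It also takes heart rate, respiratory rate, blood pressure and oxygen saturation before, during and after insertion, and a chest and abdomen film whose stated use is to confirm tube position.

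**The concern.** The protocol states which harms of this procedure are serious, then defines a complication endpoint that names none of them and closes before at least one of them could develop. Aspiration pneumonia takes time to appear and cannot be expected on a film taken directly after insertion. A pneumothorax or a bleed that follows an airway misplacement may also show later.

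Complications are one of the three components of the hypothesis. Under the listed outcomes, a patient whose tube entered the trachea and who later develops a pneumothorax counts the same as one whose misplacement had no consequence. A patient who aspirates during repeated attempts may count as having no complication. A result of no difference in complications would then describe mostly local and mechanical events, while readers would take it as a finding on safety.

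**Working it through.** The point concerns how an outcome is defined, so the plan has no figure to reproduce. The first step compares the text with itself. The second asks what the added events could show at this sample size.

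**Step 1. Events named as serious against what the plan collects**

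| Event (Introduction) | Listed in 2.2.8? | Could it be noted elsewhere? | Inside the window? |
|---|---|---|---|
| Pneumothorax | No | Chest film, vital signs, open form entry, if acute | Only if early |
| Pulmonary hemorrhage | No; bleeding is defined by the tube and the nasal or oral mucosa | Vital signs, film or open entry, if acute | Only if early |
| Aspiration pneumonia | No | Not at the time of the film | No |
| Airway misplacement | Yes, as tracheal insertion on X-ray | Also seen on the film | Yes |

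None of the three serious events is a listed outcome. Two might be picked up if acute, without any instruction to do so. One lies outside the window by its nature.

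**Step 2. What recording them could show**

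Inputs:
- Total of 39 patients in three groups (sections 2.9 and 2.10).
- Arm size. Section 2.9 gives 13 controls and 26 in each intervention group, but 13 + 26 + 26 = 65, not 39. I assume 39 / 3 = 13 per arm and show 26 as well. That discrepancy is a separate matter and does not change this point.
- Rates of the serious events are not in the document. I assume 0.5% to 5% for illustration.
- Tracheal misplacement in the cited Taiwan study: 3 among 104 patients = 2.9%.

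Upper limit of the two-sided 95% Clopper-Pearson interval with zero events, 1 − 0.025^(1/n):
- n = 13: 1 − 0.025^(1/13) = 24.7%
- n = 26: 1 − 0.025^(1/26) = 13.2%
- n = 39: 1 − 0.025^(1/39) = 9.0%

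Chance of at least one event among all 39, 1 − (1 − p)^39:

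| Assumed rate p | 0.5% | 1% | 2% | 3% | 5% |
|---|---|---|---|---|---|
| Chance of at least one | 18% | 32% | 55% | 70% | 86% |

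Comparing two arms of 13 with Fisher's exact test, if one arm has no events the other needs 5 of 13 to reach P < 0.05 (P = 0.039).

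Expected tracheal insertions at the cited rate: 39 × 3/104 = 1.1 in the trial and 13 × 3/104 = 0.4 per arm.

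So the added events can be described but not compared between arms. This is a reason to report them without a test. It is not a reason to leave them unrecorded.

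**The case against.** The case on the other side has weight.

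- **The aim is effectiveness.** The primary outcome is first-attempt success, and complications are defined as those tied to the insertion technique. A window that closes at the confirming film fits that definition. The safety wording is motivation, put as a possibility. This stands: a conclusion limited to immediate insertion complications is legitimate.
- **Acute events are not invisible.** The form has an open complications entry, vital signs are taken before, during and after insertion, a chest film is made, and tracheal insertion is recorded. This also stands. A reader might infer that the plan would record none of the three serious events. The text does not support that, because an acute one could be noted. What is missing is any instruction to look for it.
- **The Introduction is background.** It lists hazards, some of which concern a tube in use and not its insertion, and it promises no outcome set. That is true in part, but the three events are the ones the protocol itself marks as serious, and complications are in the hypothesis.
- **A journal article condenses the full protocol.** General surveillance of serious events may be described there. But this article is not silent: it fixes a list and an end of follow-up, the latter in two places that agree. The finding concerns that stated rule.
- **Little comparative gain, and weak attribution.** With about 39 patients the arms cannot be compared on rare events. Pneumonia has a background rate in ventilated patients. After more than three attempts another method may be used, which blurs attribution further. All of this stands. It limits what can be claimed from the added data and is reflected in the fix.

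**Conclusion.** The point holds in a limited form. The complication endpoint covers immediate local and mechanical events plus tracheal insertion. It does not list the three events that the protocol calls serious and fatal, and delayed events fall outside its window. The trial can support a statement on immediate insertion complications, but not an unqualified statement on which technique is safe.

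A reader might go further and infer that the trial can say nothing about safety. The documents do not support that: immediate complications, vital signs and airway misplacement are all collected. The primary endpoint is unaffected.

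On size: even once recorded, zero events would leave true rates of up to 24.7% in an arm of 13 and 9.0% in all 39 compatible with the data. These limits assume equal arms of 13; with 26 in an arm the limit is 13.2%. The document gives no rate for the serious events, so the chance of seeing any of them (18% to 86% for assumed rates of 0.5% to 5%) is illustrative only. The view that aspiration pneumonia cannot appear within the window rests on the X-ray being taken directly after insertion, as section 1.2.8 states.

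**What to change.** 1. In section 2.8, add pneumothorax, pulmonary hemorrhage and bronchoaspiration or aspiration pneumonia to the recorded adverse events.
2. Record any pleural or pulmonary finding on the chest and abdomen film that is already taken.
3. Where feasible, extend F1 in Table 1 to a fixed period, set in advance by the investigators and identical in all arms, read from the routine ICU record with no extra imaging. Change the window in section 2.2.8 to match.
4. Note which patients moved to another insertion method after failed attempts, so that later events can be read with that in mind.
5. Report these events per arm descriptively, with exact intervals and no significance test.
6. Limit the safety conclusion to what the window covers. If F1 cannot be extended, keep items 1 and 2 for acute events and word the conclusion as one on immediate insertion complications.

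The cost is protocol wording, a few lines on the form and one chart review per patient (39 charts), with no added procedure. The downside is that late pneumonia is not specific to the insertion technique in ventilated patients, so such events need cautious reading.
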